#### 3.2 SECONDARY OBJECTIVE

**3.2.1** Evaluate the antitumor effect of adoptively transferred CD8+ antigen-specific CTL clones following fludarabine-mediated lymphodepletion

### 4. STUDY DESIGN

This will be a single center, phase I, open-label, nonrandomized study in 12 individuals with metastatic melanoma (Stage IV disease). Antigen-specific T cells targeting one of the A2 or A3-restricted epitopes of the melanoma-associated antigens listed in Table 1 (Appendix A ) will be generated in vitro.

Patients will receive T cell infusions according to the following schedule:

[figure not shown]

Protocol 1796.00

Antigen-specific CD8+ T cell clones will be administered at a dose of  $10^{10}$  cells/m^2 for both Infusions #1 and #2. The median survival of transferred antigen-specific CTL clones in the presence of low-dose IL-2 (250,000 U/m^2) is approximately 17 days. By the end of 21 days, the frequency of transferred CTL is < 0.1% of the total CD8+ population. Fludarabine 25 mg / m^2 will be administered intravenously daily for 5 days prior to the second infusion of antigen-specific CD8+ CTL clones which will also be administered in the presence of low-dose IL-2. Four weeks after the second infusion, patients will be re-evaluated clinically and radiographic to determine the response to therapy. Serial blood draws during this time will allow us to determine if fludarabine lymphodepletion contributed to a prolongation of the median T cell survival beyond the expected 17 days seen with low-dose IL-2 alone.

If serious toxicity related to the T cell infusions is observed following infusion of CTL clones, , a regimen of corticosteroids will be given, and no further T cell infusions will be administered to the patient.

Subjects will be carefully monitored at regular intervals for a total of approximately 9 months following the last infusion. Evaluations after this time will be carried out by the referring physician who will be asked to notify us of the patient's progress. Peripheral blood from the patient will also be drawn. Patients receiving T cells will have up to approximately 4 tablespoons of blood drawn immediately prior to each infusion, 24 hours after each infusion, and then at specified intervals for 4 weeks from the last infusion (Appendix D). Samples will be used to evaluate the duration of in vivo persistence, function and trafficking of infused T cell clones. As a secondary objective, the residual measurable disease in these patients will also be followed to assess the therapeutic efficacy, if any, of these infusions. The estimated time to completion of the study is 24 months.

## **5. PATIENT ELIGIBILITY**

### **5.1 Inclusion Criteria**

- 5.1.1** Histopathological documentation of melanoma concurrent with the diagnosis of metastatic disease.
- 5.1.2** Male or female subject, 18 to 75 years of age
- 5.1.3** Expression of HLA-A2 or A3 as determined by FHCRC HLA typing lab.
- 5.1.4** Karnofsky Performance status of at least 80% (Appendix B) and an expected survival of greater than 6 months
- 5.1.5** Bi-dimensionally measurable disease by palpation on clinical exam, or radiographic imaging (X-ray, CT scan).
- 5.1.6** ANC >2,000/ $\mu$ L and platelet count >100,000/ $\mu$ L (at the time of first T cell infusion).

## **5.2 Exclusion Criteria**

- 5.2.1** Pregnant women, nursing mothers, men or women of reproductive ability who are unwilling to use effective contraception or abstinence. Women of childbearing potential must have a negative pregnancy test within two weeks prior to entry.
- 5.2.2** Serum creatinine > 2.0 mg/dL or Creatinine clearance < 60 ml/min.
- 5.2.3** Significant hepatic dysfunction (SGOT > 150 IU or > 3x upper limit of normal; bilirubin > 1.6 mg/dL; prothrombin time > 1.5 x control).
- 5.2.4** Clinically significant pulmonary dysfunction, as determined by medical history and physical exam. Patients so identified will undergo pulmonary functions testing and those with FEV1 < 1.0 L or DLco (corr for Hgb) < 45% will be excluded.
- 5.2.5** Significant cardiovascular abnormalities as defined by any one of the following:
  - congestive heart failure,
  - clinically significant hypotension,
  - symptoms of coronary artery disease,
  - presence of cardiac arrhythmias on EKG requiring drug therapy
- 5.2.6** Central nervous system metastases at time of therapy. Patients with a prior history of CNS involvement but since treated, may be considered if no evidence of CNS disease is detected at least 2 months after treatment.
- 5.2.7** Patients with active infections or oral temperature > 38.2 C within 72 hours of study entry or systemic infection requiring chronic maintenance or suppressive therapy.
- 5.2.8** Chemotherapeutic agents (standard or experimental), radiation therapy, or other immunosuppressive therapies less than 3 weeks prior to T cell therapy. (Patients with bulky disease may undergo cytoreductive chemotherapy but treatment will be discontinued at least 3 weeks prior to T cell therapy).
- 5.2.9** Concurrent treatment with steroids

**5.3** Virology testing (including HIV and Hepatitis B) will be performed within 6 months of the first T cell infusion. These will not be used as eligibility criteria but as a baseline result.

Protocol 1796.00

## 6. STUDY AGENTS

### 6.1 Antigen-specific CD8+ cytotoxic T cell clones Generation and characterization

All T cells administered will be CD8+ class I MHC-restricted antigen-specific T cell clones derived from the peripheral blood lymphocytes of metastatic melanoma patients.

Methods employed to generate and qualify CD8+ antigen-specific T cell clones for infusions are detailed in Appendix A. Briefly, T cell clones demonstrating antigen-specific cytolytic function will be selected for:

- CD3+, 8+ surface phenotype
- Class I MHC restricted lysis of antigen-expressing target cells
- Mycoplasma, fungal and bacterial sterility

## 7. INVESTIGATIONAL PLAN

### 7.1 Leukapheresis

Patients will undergo leukapheresis to obtain peripheral blood mononuclear cells (PBMC's) for the generation of antigen-specific T cells in the lab. Patients ineligible for leukapheresis because of poor venous access or patients who elect not to undergo leukapheresis but still wish to remain on the study may undergo a maximum of four weekly phlebotomies to obtain PBMC's necessary to establish T cell cultures. On each of these blood draws, 50 – 100 cc of blood will be obtained.

### 7.2 Dose And Administration

[figure not shown]

Antigen-specific CD8+ T cell clones will be administered at a dose of  $10^{10}$  cells/m^2 for both Infusions #1 and #2. The median survival of transferred antigen-specific CTL clones in the absence of exogenous factors (e.g .IL-2) is less than 7 days. By the end of 14 days, the frequency of transferred CTL is < 0.1% of the total CD8+ population. Fludarabine 25 mg / m^2 will be infused daily for 5 days prior to the second infusion of antigen-specific CD8+ CTL clones (starting on Day -7). Four weeks after the second infusion, patients will be re-evaluated clinically and radiographically to determine the response to therapy.

- 7.2.1** T cell clones from in vitro cultures will be washed three times with RPMI-Hepes solution and resuspended in 250-500 ml of 0.9% NaCl in preparation for infusion.
- 7.2.2** T cells will be infused intravenously at a rate of not more than 500cc/hour through an 18 or 20 gauge catheter inserted into a peripheral vein or through a central catheter. Intravenous tubing will be provided for T cell administration and no filters will be used in the infusion line. The infusion bag will be gently mixed every 5 minutes during the infusion.
- 7.2.3** Subjects will have vital signs obtained by the Clinical Research Center (CRC) nurse preinfusion, every 15 minutes during the infusion, at the end of the infusion and hourly for 2 hours following the infusion.
- 7.2.4** Subjects will have oxygen saturation measured by pulse oximetry preinfusion, immediately post infusion and 2 hours post infusion.
- 7.2.5** Subjects will receive T cell infusions through the General Clinical Research Center (University of Washington).

### **7.3 Tumor Biopsy (Optional)**

Patients undergoing surgery to remove or biopsy tumor as part of the usual management of their disease will be asked to consent to the use of a nondiagnostic portion of the tumor of the tumor for research purposes.

Patients may additionally be asked to consent to undergo a tumor biopsy for research purposes only should the tumor be accessible (e.g. skin or subcutaneous site) and risks in the opinion of the surgeon are minimal. New tumors may be biopsied when they appear following T cell infusion. Persistent tumors may be biopsied three weeks or longer following the last T cell infusion.

## **7.4 Management of Toxicities and Complications**

### **7.4.1 Criteria for Removal of Patient from the Study**

Toxicity grading will be evaluated according to guidelines in NCI Common Toxicity Criteria (66). If any patient develops grade 3 or higher toxicity related to the T cell therapy, no further infusions will be given to that patient and a regimen of corticosteroids will be given to patients.-

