#### **Exceptions:**

The following toxicities are excluded as dose-limiting:

- i. Fever > 40C for less than 24 hours
- ii. WBC < 1000 for less than 4 weeks
- iii. Platelets < 50,000 for less than 4 weeks
- iv. ANC < 500 for less than 4 weeks
- v. Lymphocytes < 500 for less than 4 weeks

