#### **7.4.4 Potential Toxicities Warranting Ablation of Adoptively Transferred Cytotoxic T Cell Clones**

The following will be considered Dose-Limiting Toxicities (DLT):

- a. Ophthalmologic: Patients receiving T cells targeting tyrosinase, MART-1 or gp100 will undergo a pre-therapy ophthalmologic exam and particular attention in the post-infusion monitoring period be given to ocular toxicity. The presence of retinitis or choroiditis as determined by ophthalmologic exam will be coded as a grade 3 toxicity and will warrant administration of steroids to ablate transferred T cells. If symptoms of visual field impairment arise, a formal visual fields examination will be conducted to determine if such a visual field defect exists. Any defect in the visual field will warrant T cell ablation.
- b. Grade 2 or greater allergic reaction of: asymptomatic bronchospasm, or generalized urticaria
- c. Grade 3 or greater toxicity (NCI Common Toxicity Criteria (66)) occurring in any other organ system following administration of antigen-specific cytotoxic

T cells and not attributable to underlying metastatic melanoma or other identifiable cause and excepting :

- i. Fever > 40C for less than 24 hours
- ii. WBC < 1000 for less than 4 weeks
- iii. Platelets < 50,000 for less than 4 weeks
- iv. ANC < 500 for less than 4 weeks
- v. Lymphocytes < 500 for less than 4 weeks

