#### **7.4.5 Treatment with Corticosteroids**

- a. Patients will receive corticosteroids if treatment-related toxicity warranting ablation of T cells is observed
- b. All patients will be hospitalized for the first 48 hours for monitoring. The following dose schedule will be used:

|           |                                    |
|-----------|------------------------------------|
| Day 1     | Intravenous Solu-Medrol at 2 mg/kg |
| Day 2     | Intravenous Solu-Medrol at 2 mg/kg |
| Day 3-4   | Prednisone at 30 mg po b.i.d.      |
| Day 5-6   | Prednisone at 15 mg po b.i.d.      |
| Day 7-8   | Prednisone at 10 mg po b.i.d.      |
| Day 9-10  | Prednisone at 10 mg po q.d.        |
| Day 11-12 | Prednisone at 5 mg po q.d.         |

- c. The in vivo frequency of infused CD4+ T cells will be assayed immediately prior to and 48 hours after the start of steroid therapy. If the frequency of infused CD4+ T cells as determined by peptide-tetramer and RT-PCR analysis of a clone-specific CDR3 region of the TCR at this time has not decrease to 25% or less of the T cell frequency prior to infusion, then, high-dose Solu-Medrol at 2 mg/kg will be given for an additional 48 hours before continuing with the tapering dose schedule.

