### **Definition for Dose-limiting Toxicities**

Serious toxicity is defined as Grade 3 or greater toxicity according to the Common Toxicity Scale ( Appendix C of protocol).

Protocol 1796.00

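### The patient-level bar on further T cell infusions starts at grade 3, but Section 7.4.4b makes a grade 2 allergic reaction a DLT warranting ablation, so no stated rule requires Infusion #2 to be withheld after it

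*Protocol*

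**What the plan says.** Three places in the protocol state when an individual patient must receive no more T cells.

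- Section 7.4.1: "If any patient develops grade 3 or higher toxicity related to the T cell therapy, no further infusions will be given to that patient". Steroids are then given. The list of exceptions that follows is introduced with "The following toxicities are excluded as dose-limiting".
- Appendix C, Stopping Criteria: the same sentence and the same exceptions.
- Section 4: "If serious toxicity related to the T cell infusions is observed following infusion of CTL clones", steroids are given and infusions cease. Appendix C, under its heading for the DLT definition, supplies the meaning of the term: "Serious toxicity is defined as Grade 3 or greater toxicity according to the Common Toxicity Scale".

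Section 7.4.4, whose title concerns toxicities that warrant ablation of the transferred cells, lists what counts as a DLT. Item b is "Grade 2 or greater allergic reaction of: asymptomatic bronchospasm, or generalized urticaria". Section 7.4.5a adds: "Patients will receive corticosteroids if treatment-related toxicity warranting ablation of T cells is observed". The study-level stopping counts, in Section 7.4.2.1 and again in Appendix C, refer to 7.4.4 for what a DLT is.

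**The concern.** Ablating the first cells and withholding the second dose ought to have the same trigger. For allergy they do not. Ablation and the DLT count begin at grade 2, while the bar on further infusions begins at grade 3. A patient with a grade 2 reaction after Infusion #1 has a DLT, receives high-dose steroids to remove the cells, and moves the trial toward termination. Yet no sentence says that this patient must not receive Infusion #2. What is at stake is re-exposure to 10^10 cells/m2 (Section 7.2) after an allergic DLT. Appendix C, which is the data and safety monitoring plan, also defines a DLT in one place at grade 3 and in another by reference to a list that starts at grade 2 for allergy.

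**Working it through.** There is no figure to reproduce. The check sets the thresholds side by side, then asks whether any other rule closes the gap.

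**Thresholds**

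| Consequence | Where stated | Lowest grade that triggers it for an allergic reaction |
|---|---|---|
| No further infusions for the patient | 7.4.1; Appendix C, Stopping Criteria | 3 |
| No further infusions for the patient | Section 4, with the term defined in Appendix C | 3 |
| DLT | Appendix C, Definition for Dose-limiting Toxicities | 3 |
| DLT | 7.4.4b | 2 |
| Ablation with steroids | 7.4.4 (title) with 7.4.5a | 2 |
| Counts toward stopping the study | 7.4.2.1 and Appendix C, both citing 7.4.4 | 2 |

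The other main DLT items do not show the mismatch: retinitis or choroiditis is coded as grade 3 in 7.4.4a, and 7.4.4c starts at grade 3. The gap is therefore the reactions named in 7.4.4b at exactly grade 2.

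**Consequence of the literal reading.** Two such reactions in the first 2 patients would stop the whole study under 7.4.2.1. One such reaction does not, by any stated rule, stop that patient's own second infusion.

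**Do the steroid rules block Infusion #2?** Inputs: the schedule in 7.4.5 runs 12 days, or 14 with the additional 48 hours of high-dose treatment. Appendix D puts Infusion #1 on Day 0 and Infusion #2 on Day 28.

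- A 12-day course started on Day s ends on Day s + 11. Started on Day 0 it ends on Day 11, which is 28 − 11 = 17 days before Infusion #2. Started on Day 7 it ends on Day 18, which is 10 days before.
- A 14-day course started on Day 0 ends on Day 13, which is 15 days before.

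The course can thus be over by Day 28, and the exclusion of concurrent steroids (5.2.9) need not apply.

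**Does 5.2.8 block it?** That criterion requires 3 weeks (21 days) without immunosuppressive therapy before T cell therapy. The intervals of 17, 15 and 10 days are all shorter than 21, so it would catch these courses if it applied at Infusion #2. But it is an entry criterion. The protocol's own fludarabine on Days 21 to 25 falls 28 − 21 = 7 to 28 − 25 = 3 days before Infusion #2, so it cannot hold literally at that infusion.

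**Do the discontinuation provisions block it?** Section 7.4.6 anticipates removal for significant toxicity, but it leaves the adjective undefined and is phrased as an expectation. Section 7.6.2 allows discontinuation when the investigator judges the patient too ill; a resolved grade 2 reaction need not meet that, and the item permits rather than requires. No item in 7.6 names a DLT or an allergic reaction.

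**The case against.** The best counter-argument is that Section 4 already closes the gap. Appendix C explains serious toxicity under its heading for the DLT definition, so the two terms may be meant as one. The same appendix sends the reader to 7.4.4 for DLTs. On that chain, Section 4's bar would reach a grade 2 allergic DLT. The exceptions under 7.4.1 are framed as events that are not dose-limiting, which also suggests that a DLT was the intended trigger. Steroids and the end of infusions are paired as one response in Section 4, 7.4.1 and Appendix C. Finally, 7.4.5b puts ablated patients in hospital for 48 hours, which meets the serious adverse event definition in Section 11.1, so re-dosing would hardly pass unnoticed.

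Much of this stands as evidence of intent, and the intended reading is probably to stop. It does not supply the rule. The Appendix C sentence that would link the terms itself sets the limit at grade 3, so following the chain exposes the two conflicting DLT definitions without resolving them. Hospitalization makes the event visible but does not bar reinfusion.

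A reader might be tempted to go further in several ways that the documents do not support.

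- Visual-field defects: 7.4.4a says "Any defect in the visual field will warrant T cell ablation", which could seem to open the same gap. The protocol assigns such a defect no grade and the toxicity criteria are not at hand, so whether it falls below grade 3 cannot be settled.
- Section 7.6.7: it ties an individual's discontinuation for grade III or IV toxicity to 7.4.2, whose criteria are study-level. The reference was apparently meant to be 7.4.1, and the matching item in Appendix C carries no such condition. This is an editorial slip in a list of potential reasons; it leaves the 7.4.1 protection intact.
- Frequency: the reports of no serious toxicity (Section 2.4.1) and no serious adverse events (Section 2.6) do not count grade 2 events. Any chance that one of the 12 patients is affected would follow wholly from an assumed rate.

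**Conclusion.** The point holds as a minor inconsistency in a safety rule. The stated bar on further infusions starts one grade above the allergic DLT that triggers ablation, and two DLT definitions coexist. Followed literally, the protocol permits Infusion #2 after a grade 2 allergic DLT; it does not direct or encourage it. The conclusion rests on reading Section 4's serious toxicity as Appendix C defines it, at grade 3 or greater, and on treating 7.4.6 and 7.6.2 as not mandatory. The affected group is limited to the 7.4.4b reactions at exactly grade 2 after the first infusion, with no rate available. No bias in the persistence comparison follows from this point.

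**What to change.** State in 7.4.1, in Section 4 and in Appendix C (Stopping Criteria) that any DLT as defined in 7.4.4 bars further T cell infusions in that patient. In Appendix C, replace the free-standing grade 3 wording under the DLT definition with a reference to 7.4.4, so that one definition serves the patient-level and study-level rules. As an editorial correction, point 7.6.7 to 7.4.1.

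The cost is amendment wording and possibly one fewer evaluable pair. Under the assumptions in Section 12.1 (difference 4 days, SD 2 days, taken here as the SD of the within-patient difference), the one-sample t-test at two-sided 0.05 has power 0.99999 with 12 pairs and 0.99996 with 11. The 95% confidence interval half-width, t(0.975, n − 1) × 2/√n, goes from 1.27 to 1.34 days. The lost pair would be of doubtful value anyway, because the steroids are given to remove the cells whose survival Infusion #1 is meant to measure.

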#### **Exceptions:**

The following toxicities are excluded as dose-limiting:

- i. Fever > 40C for less than 24 hours
- ii. WBC < 1000 for less than 4 weeks
- iii. Platelets < 50,000 for less than 4 weeks
- iv. ANC < 500 for less than 4 weeks
- v. Lymphocytes < 500 for less than 4 weeks

### **7.4.2 Criteria for Discontinuation of Study**

#### **7.4.2.1 Dose-Limiting Toxicity (DLT)**

If there exists sufficient evidence to suggest that the true DLT rate is in excess of 30%, the study will be terminated for safety reasons. (See Statistical Considerations, Section 12.2)

The study will be discontinued if

Dose-limiting toxicity (DLT) – (see section 7.4.4) is seen in

- 2 of the first 2 patients
- 3 of the first 5 or fewer patients
- 4 of the first 8 or fewer patients
- 5 of the first 10 or fewer patients
- 6 of the first 11 or fewer patients

#### **7.4.2.2 ‘Rampant’ or ‘Rapidly Progressive’ Disease**

‘Rampant’ or ‘Rapidly Progressive’ Disease following immunosuppressive therapy has been described anecdotally in patients with metastatic melanoma undergoing nonmyeloablative allogeneic stem cell transplantation and is believed to be the result of severe and prolonged immunosuppressive therapy. In contrast to patients receiving a single course of fludarabine, such patients received high-dose cyclophosphamide followed by prolonged immunosuppression with cyclosporine, MMF and/or steroid therapy. It is therefore unlikely that ‘rampant’ disease progression will be observed during the course of this study as a result of a single course of fludarabine. It is more likely that disease progression in patients on this study represents the natural history of refractory metastatic melanoma in which the average time to progression ranges from 2.4-4.9 months (67, 68). However, as a precautionary safeguard, interim analysis will be performed on the first 6 patients completing the study to Day 49. If

on Day 49 a three-fold increase in the sum of all measurable lesions (69) is observed compared to pre-treatment lesions in 4 or more of 6 patients, then the study will be suspended while the data is reviewed by an ad hoc Data Safety Monitoring Board consisting of at least two clinical investigators not associated with this study and a biostatistician. No additional patients will be treated until a decision is rendered by the Board as to whether the study should or should not continue.

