## **7.6 PREMATURE DISCONTINUATION**

Subjects who do not complete the study medication will be considered to have prematurely discontinued the study. The reasons for premature discontinuation (for example, voluntary withdrawal, toxicity, death) must be recorded on the case report form. A subject may re-enter the study after premature discontinuation only by approval of the Principal Investigator. If possible, final study evaluations should be completed at the time of discontinuation. Potential reasons for premature discontinuation include:

**7.6.1** The development of a life-threatening infection.

**7.6.2** Judgment of the principal investigator that the patient is too ill to continue.

**7.6.3** Patient noncompliance with study therapy and/or clinic appointments.

**7.6.4** Pregnancy.

**7.6.5** Voluntary withdrawal; a patient may remove himself/herself from the study at any time without prejudice.

**7.6.6** Significant and rapid progression of melanoma requiring alternative medical or surgical intervention including, but not limited to, the development of CNS metastasis.

**7.6.7** Grade III or IV toxicity judged to be possibly or probably related to study therapy and fulfilling the stopping criteria as described in 7.4.2.

**7.6.8** Termination of the study by the principal investigator, the Institutional Review Office or the Food and Drug Administration.

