##### **8.2.1 Clinical Response.**

Radiographic imaging and clinical assessment of residual disease will be compared with pre-infusion assessment. A complete response will be defined as total regression of tumor, a partial response as 50% or more regression of the sum of the perpendicular diameters of all measurable disease, a minor response as less than 50% regression. This assessment will be performed at 4 and 8 weeks following the last infusion and then every 3 months until disease progression or intervening therapy.

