|                             | Day +7                               | x                            |                                | x                     | x              | x                 | x           |                                |
|                             | Day+ 14                              | x                            |                                | x                     | x              | x                 | x           |                                |
| Pre-infusion
Fludarabine | Day +21                              | x                            | IV placement
Administer FLU | x                     | x              | x                 | x           |                                |
| Pre-infusion
Fludarabine | Day +22                              | x                            | IV placement
Administer FLU |                       | x              |                   |             |                                |
| Pre-infusion
Fludarabine | Day +23                              | x                            | IV placement
Administer FLU |                       | x              |                   | x           |                                |
| Pre-infusion
Fludarabine | Day +24                              | x                            | IV placement
Administer FLU |                       | x              |                   |             |                                |
| Pre-infusion
Fludarabine | Day +25                              | x                            | IV placement
Administer FLU |                       | x              |                   | x           |                                |
|                             | Day +26                              |                              |                                |                       | x              |                   |             |                                |
|                             | Day +27                              |                              |                                |                       | x              |                   |             |                                |
| INFUSION #2          | Day+ 28
Pre-Infusion             | x                            | IV placement                   | x                     | x              | x                 | x           |                                |

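### The rapid-progression suspension rule reads tumour size on Day 49, when no staging is scheduled, and counts only patients who reach Day 49, so selective early loss of fast progressors makes it less likely to trigger

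*Protocol*

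**What the plan says.** Section 7.4.2.2 sets a study-level safeguard against accelerated disease after immunosuppression, and Appendix C repeats it.

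- **Who is counted:** "interim analysis will be performed on the first 6 patients completing the study to Day 49".
- **What is read:** "on Day 49 a three-fold increase in the sum of all measurable lesions (69) is observed compared to pre-treatment lesions".
- **Trigger:** an increase of that size "in 4 or more of 6 patients, then the study will be suspended while the data is reviewed" by an ad hoc board. No further patients are treated until the board decides.

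Tumour assessment is timed elsewhere:

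- Appendix D puts the second infusion at "Day+ 28 Pre-Infusion". It marks staging at Day 0 and in the Day 56 row, with a window to Day 70. The Day 49 row has vital signs and blood draws but no staging mark.
- Section 4: "Four weeks after the second infusion, patients will be re-evaluated clinically and radiographic to determine the response to therapy". Section 7.2 gives the same timing.
- Section 8.2.1: "This assessment will be performed at 4 and 8 weeks following the last infusion". Section 10 agrees.

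Section 7.6 lists, among potential reasons for premature discontinuation, "Significant and rapid progression of melanoma requiring alternative medical or surgical intervention". For patients who stop early it adds: "If possible, final study evaluations should be completed at the time of discontinuation". Appendix C repeats both.

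**The concern.** Two features of the rule work against its purpose.

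First, a site that follows the schedule reaches Day 49 with no staging result to put into the rule.

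Second, the denominator depends on the outcome. A patient whose disease grows fast enough to cause death or withdrawal before Day 49 has not completed to Day 49. Nothing in 7.4.2.2, 7.6 or Appendix C says that such a patient counts as an event or holds one of the six places. Read literally, the place goes to the next patient who does complete.

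No other study-level rule fills the gap. The dose-limiting toxicity definition in 7.4.4(c) excludes toxicity attributable to the underlying melanoma, so rapid progression would not normally move the boundaries in 7.4.2.1. Under 11.3, serious events judged unrelated to treatment reach the IRB only at annual renewal. At stake is whether the first six patients can give the warning that the rule was written to give.

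**Working it through.** **Timing.** Inputs are from Appendix D and sections 4, 7.2, 8.2.1 and 10.

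- Fludarabine starts on Day 21 and the second infusion is on Day 28.
- Four weeks after the second infusion: 28 + 28 = Day 56. Eight weeks: 28 + 56 = Day 84.
- Day 49 is 49 − 28 = 21 days, or three weeks, after the second infusion.
- From Day 49 to the scheduled staging window: 56 − 49 = 7 days at the earliest, 70 − 49 = 21 days at the latest.
- Section 12.1 describes a two-week gap between infusions. That would put the four-week assessment at 14 + 28 = Day 42, which is not Day 49 either.

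**Trigger probability.** The protocol states no operating characteristic for the 4-of-6 rule, so there is no figure to reproduce. For six independent patients with event rate π among those counted:

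P(4 or more of 6) = 15π⁴(1−π)² + 6π⁵(1−π) + π⁶

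**Effect of counting completers only.** Let p be the true share of patients with progression of this size, q the share of them who leave before Day 49, and r the share of other patients who leave before Day 49. The rate among completers is

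π = p(1−q) / [p(1−q) + (1−p)(1−r)]

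With r = 0 this is p(1−q)/(1−pq). The protocol gives none of p, q or r; all values below are assumptions.

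For p = 0.5 and r = 0:

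| q | π among completers | P(4 or more of 6) |
|---|---|---|
| 0 | 0.500 | 22/64 = 0.344 |
| 0.25 | 0.375/0.875 = 0.429 | 0.221 |
| 0.50 | 0.25/0.75 = 0.333 | 73/729 = 0.100 |
| 0.75 | 0.125/0.625 = 0.200 | 0.017 |

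Other true rates, r = 0:

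| p | q = 0 | q = 0.25 | q = 0.50 | q = 0.75 |
|---|---|---|---|---|
| 0.3 | 0.070 | 0.034 | 0.011 | 0.001 |
| 0.6 | 0.544 | 0.400 | 0.221 | 0.051 |
| 0.7 | 0.744 | 0.619 | 0.418 | 0.138 |

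**Loss of other patients as well.** With p = 0.5, q = 0.5 and r = 0.25, π = 0.25/(0.25 + 0.375) = 0.40 and P = 0.179, against 0.100 when r = 0. If q = r, then π = p and there is no bias. The effect comes from losing fast progressors more often than others.

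**Delay.** With r = 0, about 6/(1−pq) patients must be treated to obtain six completers. For p = 0.5 that is 6.9, 8.0 or 9.6 of the planned 12 at q = 0.25, 0.50 or 0.75.

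**The case against.** Several stronger readings are tempting, and the protocol does not support them.

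**That the rule cannot be evaluated at all.** Day 49 is an existing visit, and 5.1.5 allows measurable disease to be established by palpation, so some lesions could be measured then without a scan. Appendix D is also not exhaustive: it omits the later tumour assessments of 8.2.1, the eye examination of 7.4.4 and the IL-2 course. The schedule diagrams in sections 4 and 7.2 are not available in the text. Still, the narrative sections agree with Appendix D on four weeks after the second infusion, and no available passage arranges a Day 49 measurement other than the rule that needs it.

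**That the patients the rule targets all drop out of it.** Section 7.6 lists potential reasons, and the progression item applies only where other intervention is needed. A patient whose lesions triple and who stays to Day 49 counts, if measured. Eligibility requires Karnofsky status of at least 80% and expected survival above six months, and Day 49 is only 28 days after fludarabine starts. The loss may be small. The evaluation at discontinuation could recover some readings, but it is not obligatory and not tied to the rule.

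**That this is the only safeguard.** Patient-level removal, adverse event reporting, investigator monitoring and the right to terminate (13.3) also exist. It is the only formal study-level rule for accelerated disease that the protocol contains.

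**That the probabilities estimate the actual loss.** They do not; they show direction and a range under assumed inputs. The protocol itself considers such progression unlikely.

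**Conclusion.** The point holds in a limited form. The rule's assessment day conflicts with the protocol's own staging schedule by 7 to 21 days. Its completer denominator also biases it toward not triggering whenever fast progressors leave before Day 49 more often than other patients.

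The direction needs only that differential loss. The size cannot be fixed from the protocol. At an assumed true rate of 50%, the trigger probability of 0.34 becomes 0.22, 0.10 or 0.02 for early losses of 25%, 50% or 75% among rapid progressors with none among others. Losing 25% of other patients as well raises the middle figure to 0.18.

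This is a defect in a decision rule that the protocol states in full, not a detail left for a later analysis plan. It does not show that the rule is unusable or that it would miss every case.

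**What to change.** Make the same changes in section 7.4.2.2 and in Appendix C. The three-fold and 4-of-6 thresholds need not change.

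1. Define the six as consecutive patients who start fludarabine. Those who die or are withdrawn for progression before the assessment then stay in the denominator and are not replaced.
2. State the convention for counting those patients, because the result depends on it. With p = 0.5 and q = 0.5, counting them as events gives π = 0.5 and P = 0.344. Keeping them in the six as non-events gives π = 0.5 × 0.5 = 0.25 and P = 154/4096 = 0.038, below even the 0.100 of the present rule.
3. Reconcile the Day 49 reading with Appendix D and sections 4, 7.2, 8.2.1 and 10, so that a scheduled measurement feeds the rule. Which day stands is for the sponsor to decide.

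**Cost.** If the existing staging is used, only wording changes, but the review reads 7 to 21 days later than now written. If Day 49 is kept, a lesion measurement has to be added to the schedule. Counting early progression withdrawals as events would let some natural-history progression contribute to the trigger; the protocol cites an average time to progression of 2.4 to 4.9 months. A trigger is not trivial, since treatment of new patients stops until the board decides, but it does not end the study.
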